### Trial design {8}

The Telemechron study was designed as a multi-centre, open-label, randomised, superiority study with two parallel groups and a 1:1 allocation ratio. This study design was chosen over others because RCTs are considered the best type of study design to evaluate the effectiveness of health interventions [19].

## Methods: participants, interventions and outcomes

### Study setting {9}

The participants are recruited in the diabetic outpatient clinics of the Hospitals of Rovereto and Trento, which are the most relevant diabetic clinics of PAT for diabetic individuals, with an average of 30 visits per day at Rovereto, and 40 visits per day at Trento. In the Province, the prevalence of T2DM is estimated to be 5.0%. This is slightly lower prevalence than the one estimated nationally (i.e. 6.2%) [17].

### Eligibility criteria {10}

Participants must meet at randomisation all the inclusion criteria and none of the exclusion criteria listed in Table 1.

**Table 1 Tab1:** Inclusion and exclusion criteria

Inclusion criteria	Exclusion criteria
• Being diagnosed with T2DM; • Aged ≥ 18 and ≤ 85 years old; • Having an HbA1c level > 7% (53 mmol/mol) and < 12% (108 mmol/mol); • Being able to walk without walking aids; • Having provided written informed consent; • Having a smartphone or a tablet and being able to download the App that will be used to insert the required data	• Having a BMI < 18 kg/m^2^ and > 45 kg/m^2^; • Having a sBP < 100 or > 200 mmHg and/or dBP < 50 or > 120 mmHg; • Being diagnosed with a stage 5 CKD^a^ • Being diagnosed with a NYHA stage IV; • Poor collaboration (i.e. unwilling to modify the actual plan of control and therapy, even if not ideal) for which adherence to the study is unlikely • Having no possibility of using a smartphone or a tablet • Having medical conditions affecting the study participation (i.e. life expectancy < 1 year)

*Abbreviations*: *BMI* body mass index, *CKD* chronic kidney disease, *dBP* diastolic BP, *HbA1c* glycated haemoglobin type A1c, *NYHA* New York Heart Association, *T2DM* type 2 diabetes mellitus, *sBP* systolic BP

^a^based on the glomerular filtration rate according to the CKD-Epidemiology Collaboration equation < 15 ml/min/m^2^ accounting for individual body surface [20]

### Who will take informed consent? {26a}

Potentially eligible participants are identified during diabetes clinic appointments, either face-to-face or via a remote appointment (phone call). Clinicians of the diabetes clinics will provide standardised and key information regarding the study. If patients are interested, they will receive the information sheet to read (either face-to-face or by email). The information sheet and the consent form for the participants are originally written in Italian. At this stage, patients will be contacted by a member of the research team (registered nurse) who will also ensure that the information sheet is fully read and understood. During another dedicated face-to-face appointment, the patient who volunteers to participate in the study will provide written informed consent, provided that all questions regarding his or her involvement in the study are answered. Clinicians are responsible to sign the informed consent form with the patient during this visit.

### Additional consent provisions for collection and use of participant data and biological specimens {26b}

In addition to the informed consents for the study, the researchers collect the informed and specific consents for the personal data processing activities. In fact, the processing of personal data of this research should comply with the General Data Protection Regulation (Regulation 2016/679 or “GDPR”) and the Italian Data Protection Code (*Decreto Legislativo*—D.Lgs 101/2018) [21, 22]. The privacy policy has been elaborated under Articles 12 and 13 of the GDPR. The legal grounds of the processing are both the explicit consent of the data subjects (as regards data concerning health) and the performance of tasks carried out in the public interest by the data controller.

By signing the informed consent, participants will allow the appointed researchers to access their medical records’, including blood test results at follow-up. Blood tests are carried out by qualified nurses who are not part of the research team but are still part of the APSS organisation. Blood tests performed within the hospital organisation do not require additional written consent.

## Interventions

### Intervention description {11a}

After being approached for face-to-face screening and enrolment, eligible individuals are randomised on a 1:1 allocation ratio to the intervention or the control group.

Those allocated to the intervention group are prescribed with the TreC Diabete App. This is one of several Apps created within the so-called TreC platform, which enables citizens from PAT to access, manage and share information about their health and wellbeing in the context of telemedicine [23–26]. TreC is an acronym for *Cartella Clinica del Cittadino* (Citizens’ Clinical Records), in which the citizen/patient plays the role of the focal manager and owner of his/her own health data. The technological platform has been preliminarily used for other studies targeting patients with diabetes, specifically pregnant women [27].

Participants will download the App from Google Play or Apple Store (Android or iOS system, respectively), accept the online information form, enter their tax code (*Codice Fiscale*) and the health card number, create a PIN code and then confirm it to complete the procedure. At this point, the participant must wait for the clinician to proceed with the activation of the App; otherwise, it will not be possible to access the functions. Participants are enabled to activate the App as soon as the clinician provides the unique activation code. Participants can then set a personal password, required to access the App.

Clinicians will then prescribe the App for a 12-month period through the online medical dashboard. The dashboard allows the visualisation of the information shared by the participant. Moreover, it enables healthcare staff to interact directly through video-chat and chat with the participant. A menu allows clinicians to set up a specific and personalised plan for each participant: they are asked to indicate which parameter (e.g. BP) should be registered in the App and to activate reminders at set intervals. During the 12-month follow-up, clinicians will regularly check the information entered by the participant (minimum frequency of 45 days). Clinicians can provide advice based on the information shared by the participant (e.g. inviting the participant to book an appointment with their general practitioner—GP). Participants will receive the training for the use of the App as soon as they are allocated to the intervention group. A member of the research team (registered nurse) will show the participant how the App works, highlighting its different features. The appointed person will specifically show how to enter the PIN when asked, insert different types of data in the App, write in the chat, and fill in the questionnaire. Also, the registered nurse could be contacted by phone in case of problems managing the app. The app’s chat was another way to contact researchers and IT personnel to solve management problems. Paper-based training material can be provided to the participant upon request.

Table 2 depicts the App features (for the prescriber and the participant perspectives) and provides an explanation of their use.

**Table 2 Tab2:** TreC Diabete App features and related description

Level	Feature	Description
Dashboard (prescriber)	Activation of credentials for the participant	The feature allows to activate the App for a specific participant and is performed by the clinicians via dashboard
Dashboard (prescriber)	Setup of the data each participant will be required to enter into the App	The feature allows the clinician to decide which data the participant will be asked to enter by the App. It allows the storage of the data and the sharing of information
Dashboard (prescriber)	Display of data	The feature allows the user to view the data as entered by the participant. It allows the sharing of the information, which cannot be altered or modified
Dashboard (prescriber)	Activation and use of a chat between clinicians/healthcare staff and participants	The feature allows the user to activate a chat for remote contact and communication between clinicians and participants. Different types of information could be shared through this channel (including files and pictures)
Dashboard (prescriber)	Personalised activation of tasks based on the diabetes profile	The feature allows the clinician to assign tasks and related reminders regarding the insertion of certain parameters, such as weight, blood pressure, glycaemia, with a defined frequency, time of the day of execution and related deadlines. The function allows the memorisation and the communication of information
Dashboard (prescriber)	Setup of reminders related to drugs	The feature allows the clinicians to set reminders regarding specific drugs and healthy lifestyle behaviours. It is considered a function that allows the communication of information
Dashboard (prescriber)	Set up of a blood glucose profile	The feature allows the clinician to insert the participant’s blood glucose profile for informational purposes only
Dashboard (prescriber)	Set up of ordinary reports	The feature allows the doctor to receive regular reports produced by the App and based on the data inserted by the participant at specific intervals. The data are shown as aggregated and cannot be modified
App (participant)	Chat between clinicians and participant	The feature allows the participant to send messages to the clinician for remote contact and communication
App (participant)	Activation of the diary of personal observations	The feature allows the participant to enter and review the parameters inserted for the activated tasks. Reminders may be activated (without push notifications). Participants can enter and insert other unassigned parameters. The insertion is done directly by the participant. The diary is not directly visible to the clinician through the dashboard with the exception of the prescribed parameters
App (participant)	Activation of the drugs’ diary	The feature allows the participant to manually record the intake of drugs (either prescribed or not by the clinician)
App (participant)	Set up of reminders	The feature allows the participant to receive notifications (push) concerning telemedicine appointments

Participants in the control group are asked to record their health-related data such as body weight, BP, glycaemic levels, results of laboratory tests and diagnostic tests as usual (e.g. on a paper diary). Other information collected by the control group participants during the follow-up period can be shared, as routinely done, with their GP.

For the App functions described above and according to the Medical Device Regulation (MDR) (EU) 2017/745 requirements [2], the TreC Diabete App cannot be considered a medical device. The App does not perform operations on clinical data; it is used as data archive and for communication and simple research purposes. It does not provide direct recommendations to participants based on algorithms; it does not make changes or alterations to the collected data and it does not transfer data with implantable devices eventually belonging to the participants. Moreover, the App does not provide direct recommendation to the clinicians for diagnosis and treatment; it cannot be used to handle emergency situations.

Table 3 depicts the list of the therapeutic goals that people with T2DM should reach set by the current national and international guidelines [28–31].

**Table 3 Tab3:** List of therapeutic goals as set by the current national and international guidelines [28–31]

Type of target	Values
Glycaemic target	HbA1c < 53 mmol/mol
BP target	sBP < 130 mmHg if < 65 years old sBP < 140 mmHg if ≥ 65 years old dBP ≥ 70 mmHg and < 80 mmHg
Lipid target	LDL cholesterol < 70 mg/dl non-HDL cholesterol < 100 mg/dl (if triglycerides ≥ 200 mg/dl)

*Abbreviations*: *dBP* Diastolic blood pressure, *HDL* High-density lipoproteins, *LDL* Low-density lipoproteins, *sBP* Systolic blood pressure

### Explanation for the choice of comparators {6b}

Both the intervention and control group will receive the best care for T2DM, in line with the integrated preventive and diagnostic care pathway (called “*Percorso Preventivo Diagnostico Terapeutico Assistenziale*—PPDTA” in Italian) which is available in Italian upon request to the authors of this manuscript. An appointment with the outpatient diabetes clinic staff is scheduled at 6 and 12 months from the first visit (taking place within 30 days of the study entry), either through telemedicine (remote visit) or face-to-face for all participants.

### Criteria for discontinuing or modifying allocated interventions {11b}

Participants can leave the study at any time and for any reason if they wish to do so.

### Strategies to improve adherence to interventions {11c}

Adherence to the study will be monitored by the research team and clinicians. Study participants allocated to the intervention group will receive set up reminders through the App regarding the tasks that need to be done (e.g. measure and record the blood sugar level). Adherence to the study will be monitored by the research team and clinicians, as usage and interaction by the participant with the App can be checked through the dashboard. Scheduled visits at the diabetes centres can also be an opportunity to discuss possible difficulties in using the App and to remind participants why it is important to regularly record their data.

### Relevant concomitant care permitted or prohibited during the trial {11d}

Concomitant care is permitted in line with the local standard practice. In case of relevant care actions (e.g. emergency), data are recorded in line with the standard procedures as part of the patients’ record.

### Provisions for post-trial care {30}

Post-trial care is delivered in line with the local standard practice.

### Outcomes {12}

#### Primary outcome measure

Difference in the participants’ HbA1c level between the two arms at 12 months. Blood tests, including HbA1c level, are carried out by qualified nurses and processed by the local analysis laboratory. Blood tests results are automatically registered on the Hospital Information System (HIS) and reviewed by clinicians and research staff involved in the study.

#### Secondary outcome measures

Secondary outcome measures are collected at different time point (for specific times of data collection refer to Table 4).Proportion of participants with Hb1Ac < 53 mmol/mol within the two arms;Difference in HbA1c levels between the two arms other than at 12 months;Reporting frequency and number of new hypoglycaemic episodes within the two arms;Proportion of participants reaching the targeted lipid profile (LDL level < 70 mg/dl and non-HLD cholesterol level < 100 mg/dl) and BP levels (sBP < 130 mmHg or > 140 if ≥ 65 years old);Effect on weight, lipid profile and BP levels for the App users;Effect on physical activity performed during the last 7 days prior filling in the questionnaire, for both arm participants;Number of hospitalisation events within the two arms;Number of measurements and level of physical activity with the prescribed activities (body weight monitoring, BP measurements, physical activity) within the two arms;Changes in quality of life (QoL) scores for participants of both arms;Satisfaction and usability score of the App in the intervention arm;

**Table 4 Tab4:** Time schedule of enrolment, interventions and assessments during the study period, adapted from the example template provided by the SPIRIT Group [28]

	Enrolment		Allocation		Post-allocation			Close-out	Personnel and participant involvement	Method of data collection
Timepoint	14 to 21 days prior T0	7 to 14 days prior T0	0 months	0 months (T0)	3 months (T1) (± 30 days)	6 months (T2) (± 30 days)	9 months (T3) (± 30 days)	12 months (T4) (± 30 days)		
ENROLLMENT										
** Informal study information**	x	x							Clinician	Scheduled appointment at clinic
** Eligibility screen**	x	x							Clinician or PI	Scheduled appointment at clinic
** Informed consent signed**		x							Clinician or PI and participant	Face-to-face meeting
** Allocation**			x						Research team	Face-to-face meeting
** Blood tests prescription**		x							Clinician	Face-to-face meeting
** Provide 3 copies of IPAQ questionnaire**		x							Research team	Face-to-face meeting
INTERVENTION										
** App education and instruction manual**				x					Research team	Face to face meeting
** Inform GP of participation**				x					Clinician	Through email
** Help and support with the App use**				x	x	x	x	x	Research team	Phone- email
** App (intervention) monitoring**				x	x	x	x	x	Clinician or research team	Medical dashboard
** Medical intervention via App – data recording**				x	x	x	x	x	Clinician and participant	Medical dashboard
ASSESSMENTS: clinical and biohumoral variables and clinical indicators										
** Body weight and number of checks (previous month)**		x			x	x	x	x	Research team	Face to face meeting, medical dashboard /App or other recording tools
** Vital signs and number of checks (previous month)**		x			x	x	x	x	Research team	Face to face meeting, medical dashboard/App or other recording tools
** Demographic characteristics and clinical variables**^**a**^		x							Clinician and research team	Face to face meeting, HIS
** Hb1Ac levels and number of checks**		x			x	x	x	x	Clinician, research team, laboratory personnel	HIS
** Other blood tests**^**b**^		x						x	Clinician, research team, laboratory personnel	HIS
** Questionnaires (SF-12/MMAS-4/DASI)**				x				x	Research team, participant	Face to face meeting
** IPAQ questionnaire**				x	x	x	x	x	Research team, participant	Face to face meeting and phone call
** SUS questionnaire (App group only)**								x	Research team, participant	Face-to-face meeting
** Number of nursing and medical (tele)consultation and chat interactions**					x	x	x	x	Research team	Medical dashboard/App and HIS
** Number of unscheduled specialists visits (macro- and micro-vascular complications), number of accesses to ED for cardiac, cardiovascular or diabetic problems**					x	x	x	x	Research team	HIS
** Number of therapeutic plan changes**					x	x	x	x	Research team	Medical dashboard/App and HIS
** Time spent for (tele)consultation**						x			Research team	Recording of time during visit
** Number of hospitalisation**						x	x	x	Research team	HIS
** Number of hypoglycaemic episodes**					x	x	x	x	Research team, participants	Medical dashboard/App and/or download of data from glucometer

*Abbreviations*: *DASI* Duke Activity Status Index, *ED* emergency department, *HbA1c* Glycosylated Haemoglobin Type A1C, *HIS* Hospital Information System, *IPAQ* International Physical Activity Questionnaire, *MMSA-4* Morisky Medication Adherence Scale, *SF-12* Short Form-12, *SUS* System Usability Scale, *PI* Principal Investigator

^a^demographic characteristics: age, sex, citizenship, marital status, school level; clinical variables: diabetes diagnosis year, smoking habit, weight, height, body mass index, systolic and diastolic blood pressure, heart rate, last emergency hospital admission for cardiologic condition, retinopathy, neuropathy, acute myocardial infarction, heart failure, ischemic heart disease, previous cerebrovascular events, obliterative arterial disease in the lower limbs, chronic kidney disease, dementia, chronic obstructive pulmonary disease, rheumatologic disease, peptic ulcer, liver disease, diabetic and cardiovascular drug therapies ^b^fasting glycaemia, total cholesterol, HDL cholesterol, non-HDL cholesterol, LDL cholesterol, creatinine, eGFR (CKD-EPI), ratio albumin/creatinine on morning urine sample, triglycerides

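### The secondary blood-pressure responder outcome counts systolic pressure above 140 mmHg as reaching target at age 65 or over, which contradicts Table 3

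*Protocol article*

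**What the plan says.** Two places in the protocol article set thresholds for the same quantities.

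- **Secondary outcome measures.** One item begins "Proportion of participants reaching the targeted lipid profile". It gives the lipid rule as "LDL level < 70 mg/dl and non-HLD cholesterol level < 100 mg/dl" and the blood-pressure rule as "BP levels (sBP < 130 mmHg or > 140 if ≥ 65 years old".
- **Intervention description {11a}, Table 3 (therapeutic goals).** The systolic goals are "sBP < 130 mmHg if < 65 years old" and "sBP < 140 mmHg if ≥ 65 years old". The diastolic goal is "dBP ≥ 70 mmHg and < 80 mmHg". The lipid goals are the same LDL limit, plus "non-HDL cholesterol < 100 mg/dl (if triglycerides ≥ 200 mg/dl".

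Eligibility criteria {10} admit participants "Aged ≥ 18 and ≤ 85 years old", so the older age group is within the trial population.

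**The concern.** The outcome is worded as reaching a target, so whatever meets the listed threshold is a success. For participants aged 65 or over the listed systolic threshold is above 140 mmHg, while Table 3 sets the goal below 140 mmHg. An analyst who programs the outcome as printed would score older participants against the opposite of the stated goal.

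Control of blood pressure and cholesterol is the first item under Secondary objectives, which also promise comparisons between groups. The other listed outcome on blood-pressure level is worded for App users. The responder proportion is therefore the listed blood-pressure outcome that most directly serves the between-arm comparison. Section {17a} assigns the analysis to people not directly involved in the study, who would be likely to work from the written definition.

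**Working it through.** **No stated figure to reproduce.** The point depends on no sample size, power or significance level. It rests on comparing two sets of thresholds.

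**Step 1. The rules.** The word 'or' in the outcome allows two readings.
- Table 3: systolic < 130 if under 65; < 140 if 65 or over.
- Reading A: < 130 if under 65; > 140 if 65 or over.
- Reading B: < 130 at any age, or > 140 if 65 or over.

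**Step 2. Example values at age 70** (systolic component only).

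| Systolic (mmHg) | Table 3 | Reading A | Reading B |
|---|---|---|---|
| 125 | success | failure | success |
| 135 | success | failure | failure |
| 145 | failure | success | success |
| 150 | failure | success | success |

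At age 60 all three rules agree at every value tried (125 to 150). The conflict is confined to participants aged 65 or over. There, 135 and 150 are classified against Table 3 under both readings. This step needs no distributional assumption.

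**Step 3. Size in the older group.** The article gives no systolic distribution, so these inputs are assumptions: normal, mean 138, SD 15, and an App effect that lowers the mean by 5 to 133. Φ is the standard normal distribution function.
- Table 3, Φ((140 − mean)/15): Φ(2/15) = 0.553 and Φ(7/15) = 0.680. Change +12.7 points.
- Reading A, the complement: 0.447 and 0.320. Change −12.7 points.
- Reading B, Φ((130 − mean)/15) plus the complement: 0.297 + 0.447 = 0.744 and 0.421 + 0.320 = 0.741. Change −0.3 points.

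**Step 4. Range.** The same formulas were run with starting means of 130, 138 and 145 and SDs of 12, 15 and 18, keeping the 5 mmHg reduction.
- Table 3: +8.7 to +16.2 points.
- Reading A: −8.7 to −16.2 points, always the mirror image.
- Reading B: +6.5 points (mean 130, SD 12) to −6.5 points (mean 145, SD 12), and −0.5 to −0.2 points at mean 138. In each of the nine cases it is below the Table 3 change.

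**Step 5. The other differences from Table 3.**
- Lipids: LDL 65, non-HDL 105 and triglycerides 150 mg/dl meets Table 3 but fails the outcome rule. With triglycerides 210 it fails both. The outcome rule is stricter than Table 3 only when triglycerides are below 200.
- Diastolic: Table 3 has a range; the outcome has no diastolic component.

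**The case against.** The strongest reply is that this is a one-character slip. The sentence speaks of reaching a target, pairs the clause with a less-than threshold, and shares its cut-off and age limit with Table 3, so a careful analyst would notice. That is probably how it arose. It still stands in the current outcome definition, and no other section corrects it.

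A reader might infer that the endpoint simply runs backwards, so that benefit would always be reported as harm of equal size. The article does not support that. The equal and opposite effect belongs to reading A alone. Under reading B the outcome becomes close to uninformative at the central inputs, and elsewhere in the range it is diluted or moderately reversed. What survives both readings is the misclassification of values such as 135 and 150.

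A reader might also treat the missing diastolic range and triglyceride condition as errors of the same kind. They are not. Table 3 lists guideline goals within the intervention description, and the outcome item does not cite it. A systolic-only responder, or a non-HDL limit applied to everyone, is a coherent rule that can be programmed and applies equally to both arms. These details could also sit in an analysis plan that is not shown. What remains is that the outcome refers to a targeted profile while departing from the only full list of targets in the article, so a clarification is reasonable.

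Finally, the reach is limited. This is part of one item in a list of secondary outcomes. The primary HbA1c endpoint and the sample size are untouched.

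**Conclusion.** The contradiction is real and needs no assumption: for participants aged 65 or over, the outcome definition and Table 3 give opposite directions at the same 140 mmHg cut-off. Under either reading of 'or', 150 mmHg is scored a success and 135 mmHg a failure at age 70.

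The size in that age group does rest on assumptions. At the central inputs, a benefit worth about 13 points under Table 3 would appear as about −13 points or about zero, depending on the reading. The effect on the whole-trial proportion cannot be stated, because the article gives no share of participants aged 65 or over; younger participants are unaffected.

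This is a definition to correct before analysis, not a threat to the trial's main conclusion. The lipid and diastolic differences are clarifications of lower weight.

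**What to change.** Reconcile the outcome item under Secondary outcome measures with Table 3, so that one systolic responder rule, with its inequality in the same direction in both places, is fixed in the protocol or analysis plan before the data are analysed. Word it by age group so that 'or' cannot be read two ways. No view is given here on which clinical threshold should apply; that is for the investigators to confirm.

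In the same amendment, state whether the responder is meant to follow Table 3 on the diastolic range and on the triglyceride condition for non-HDL cholesterol, or to depart from it on purpose.

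The cost is a sentence or two. Table 4 and its footnotes already schedule age, vital signs, LDL, non-HDL cholesterol and triglycerides, so no new data are needed. Because the trial is open-label, fixing the rule before anyone sees results by arm also avoids the appearance of a choice made after the fact.
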